## Components of the chest X-ray reporting pathway

### Reporting radiographer chest X-ray report

All reporting radiographers participating in the study have completed an accredited postgraduate certificate in adult CXR reporting (experience 1–8 years) and currently provide CXR reports in clinical practice. All CXRs referred by GP on eligible patients (aged over 16 years, no active history of lung cancer) will receive a reporting radiographer report. In line with current practice, a narrated report will be provided rather than a structured report. Image interpretation will occur on Picture Archiving and Communication System (PACS) workstations and the report entered into PACS and transferred to the patient electronic record. If the reporting radiographer requires additional investigations (repeat X-ray due to inadequate initial X-ray, additional X-ray view, CT of the chest and abdomen), these will be arranged by the reporting radiographer at time of the CXR report.

### Off-protocol radiographer reporting

Where the radiographer performing the CXR is concerned about the appearance of the X-ray or by the clinical condition of the patient, current practice at Homerton University Hospital is for the CXR to be reviewed by a reporting radiographer or a consultant radiologist prior to the patient leaving the department. This includes, for example, where the radiographer suspects a pneumothorax, tuberculosis or cancer. If a radiographer has concerns that the appearances of the CXR is abnormal and a significant pathology may be present, these patients will receive an immediate report, regardless of the reporting session allocation (immediate/standard) so as not to negatively impact on patient management. All such occurrences will be identified, included in the intention-to-treat principle, but we will also carry out sensitivity analysis excluding them. In view of randomisation, we expect the same rates of such cases in intervention and control sessions.

### Equivocal reporting radiographer reports

For cases where the reporting radiographer is unsure with the findings, and/or clinical significance of the CXR, they will be free to review the case with another reporting radiographer and/or consultant radiologist. This is in line with current best practice. This will include, for example, instances where previous cross-sectional imaging is available for the patient, or where there may be unfamiliar medical terminology on the CXR request form. All occurrences will be recorded.

### Consultant radiologist chest X-ray report

All CXRs will receive a consultant radiologist report (general radiologists; experience range 2–21 years post FRCR), blinded to the reporting radiographer CXR report. Consultant radiologist reporting will occur at the next session following the reporting radiographer report. Interpretation will occur using PACS workstations and the report will be entered into a secure database.

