### Intervention

The intervention reporting strategy is modelled on the National Optimal lung cancer pathway developed in 2016 [31]. The intervention strategy aims to streamline the patient journey through the lung cancer pathway by providing prompt interpretation of CXRs referred by general practice (GP) and offering immediate CT when appropriate.

Chest X-rays included in the intervention arm will be reported at the time of image acquisition while the patient is still in the radiology department. Patients who have a CXR suspicious for cancer will be offered an immediate CT of the chest and upper abdomen.

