### CT of the chest

Patients who have an abnormal CXR suspicious for cancer will have a CT of the chest performed. The reporting practitioner (reporting radiographer or consultant radiologist) will arrange this following standard department procedure. The CT scan forms part of routine clinical management and, therefore, does not require any additional radiation exposure. A consultant radiologist will interpret all CTs.

The CT performed will be stratified based on the CXR appearances and the likelihood of cancer. This will minimise radiation exposure, in line with best practice. For patients with a CXR that is suspicious but not categorical for lung cancer, a low-dose, unenhanced CT of the chest will be performed. For patients who have a CXR that shows a high likelihood of cancer, a CT of the chest and abdomen with intravenously administered contrast will be offered

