### Index diagnosis by thoracic radiologist

Chest X-rays that are found to have discordant reporting radiographer and consultant radiologist reports at peer review will have an index diagnosis. For cases that have undergone a subsequent CT scan of the chest and abdomen, the CT report will constitute the index diagnosis. CXR reports, either reporting radiographer or consultant radiologist, will be deemed a true positive if CT confirms the CXR diagnosis and a false positive if the CT is normal or another pathology is demonstrated. True positive and true negative will be a consensus decision and corroboration between the CT and clinical history between a respiratory physician and a thoracic radiologist. Assessment of report accuracy will be made blinded to the origin (reporting radiographer/consultant radiologist) of the CXR report.

For cases that have not had a CT performed, an independent expert thoracic consultant radiologist will constitute the index diagnosis. The index radiologist will feed back the diagnosis via a standardised proforma. All available thoracic imaging (X-ray, CT) for the patient will be sent via the Image Exchange Portal (IEP) to the Royal Brompton Hospital. IEP is an established, secure method of transferring radiology cases for external review within the NHS. A thoracic consultant radiologist will review the available imaging and provide the definite diagnosis. CXR reports, both reporting radiographer and consultant radiologist, will be deemed a true positive if the thoracic radiologist confirms the CXR diagnosis and a false positive if the thoracic radiologist interpretation is normal or another pathology is demonstrated.

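### The consultant's CXR read is masked to the radiographer's report but not to an immediate CT that may already exist, so the accuracy comparison may be tilted against radiographers

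*Protocol article*

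**What the plan says.** Four parts of the protocol article bear on this point.

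- **The consultant read** (Consultant radiologist chest X-ray report). All CXRs receive a consultant report, "blinded to the reporting radiographer CXR report". Timing: "Consultant radiologist reporting will occur at the next session following the reporting radiographer report". Platform: "Interpretation will occur using PACS workstations and the report will be entered into a secure database".
- **The radiographer read and the CT** (Intervention; Reporting radiographer chest X-ray report). Intervention films "will be reported at the time of image acquisition while the patient is still in the radiology department". For suspicious films: "Patients who have a CXR suspicious for cancer will be offered an immediate CT of the chest and upper abdomen". The reporting radiographer arranges further imaging when reporting, with "the report entered into PACS and transferred to the patient electronic record".
- **Control sessions** (Control; Off-protocol radiographer reporting). The usual route is a CT by appointment. If the radiographer taking the film is worried by it, an immediate report is made whatever the session's allocation, and a CT is offered if the findings suggest lung cancer.
- **CT reading and reference standard** (CT of the chest; Index diagnosis by thoracic radiologist). "A consultant radiologist will interpret all CTs". Only films with discordant radiographer and consultant reports receive an index diagnosis. Where such a film has had a CT, "the CT report will constitute the index diagnosis".

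**The concern.** The blinding is defined by one item, the radiographer's written report. In an intervention session, the act that follows a suspicious report can leave a second trace on the imaging system before the consultant sits down: a CT request, and possibly CT images. That trace matters in two ways. It tells the consultant that the film was called suspicious, which is the information the blinding is meant to withhold. It may also show the reference standard itself. The type of CT is chosen according to how likely cancer appears on the film, so even the kind of scan carries information.

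This is review bias in a paired reader comparison. The radiographer reads before any CT; the consultant may read after it. The Background section states an aim of evaluating radiographer reporting in comparison with radiologists. Outcome measures lists the accuracy of radiographer reporting as a secondary outcome, and the Health economic assessment uses diagnostic accuracy as an input. A tilt in the comparator could pass into all three.

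**Working it through.** The protocol gives no expected value or sample size for consultant accuracy, so there is no stated figure to reproduce. The check has two parts: the sequence of events, then an illustration of size.

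**Sequence**

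| Step | Intervention session | Control session, usual route | Control session, off-protocol |
|---|---|---|---|
| Radiographer report | patient still in department | within one working day | patient still in department |
| CT if suspicious | offered immediately | by appointment | offered if lung cancer suspected |
| Consultant CXR read | next session after the radiographer report | same | same |
| CT may exist at that read | yes | less likely | yes |

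Exposure is therefore unequal between arms, but not confined to one. The protocol expects off-protocol cases at the same rate in both arms, so the other immediate CTs in intervention sessions make the difference.

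**Direction**

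An immediate CT normally follows the radiographer's suspicious call, so it can act only on films the radiographer flagged.

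- *CT shows cancer.* A consultant who would have missed it may now call it. A radiographer-right, consultant-wrong pair becomes concordant and leaves adjudication.
- *CT shows no cancer.* A consultant who would have agreed with a false positive may now call the film clear. A concordant pair becomes discordant and is scored against the radiographer.
- *Radiographer missed the cancer.* The radiographer's read triggers no CT, so a consultant-right, radiographer-wrong pair stays as it is.

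The first two effects favour the consultant, and nothing equivalent favours the radiographer.

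**Size, as an illustration**

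Inputs:
- Cancers per arm: about 25, half of the 50 per year in Sample size.
- Radiographer sensitivity: 0.954, from the examination data in Background.
- Unaided consultant sensitivity *s*: assumed, 0.80 to 0.95.
- Share *f* of radiographer-flagged cancers in which a CT exists and guides the consultant's CXR read: assumed, 0 to 1.
- The two readers' errors are assumed independent given cancer.

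Apparent consultant sensitivity = *s* + (1 − *s*) × 0.954 × *f*. Extra cancers called = 25 × (1 − *s*) × 0.954 × *f*.

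| *s* | *f* = 0 | *f* = 0.25 | *f* = 0.5 | *f* = 1 |
|---|---|---|---|---|
| 0.80 | 0.800 (0) | 0.848 (1.2) | 0.895 (2.4) | 0.991 (4.8) |
| 0.90 | 0.900 (0) | 0.924 (0.6) | 0.948 (1.2) | 0.995 (2.4) |
| 0.95 | 0.950 (0) | 0.962 (0.3) | 0.974 (0.6) | 0.998 (1.2) |

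Extra cancers called are in brackets. Worked cell: 0.80 + 0.20 × 0.954 × 1 = 0.991, and 25 × 0.20 × 0.954 = 4.8.

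If the consultant also has sensitivity 0.954, each discordant cell for cancers holds 25 × 0.954 × 0.046 = 1.1 films when fully masked. At *f* = 1 the cell favouring the radiographer falls to 0, while the other stays at 1.1. Apparent consultant sensitivity becomes 0.954 + 0.046 × 0.954 = 0.998.

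Overall specificity hardly moves, because few cancer-free films have a CT. With radiographer specificity 0.959 and unaided consultant specificity 0.90, the largest gain is 0.10 × 0.041 × 1 = 0.004. Among radiographer false positives that do have a CT, however, apparent consultant specificity could rise to 1.0.

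**The case against.** The strongest reply is that this reads too much into a condensed article. The consultant read is declared blinded, its report goes to a separate database, and working details such as worklists belong in the full protocol. That is fair as to how blinding is operated. It does not settle its scope, which the article itself fixes: it names the radiographer's report and nothing else. The other masking in the plan hides a report's origin from those who compare and adjudicate reports; it does not mask the consultant reader.

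Several further objections stand, and they limit the point:

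- A reader might infer that consultant accuracy *is* inflated. The documents do not support that. CT is only offered, and nothing says that consultants open it when reading the CXR.
- A reader might infer that the reference standard is always in view. No timing is given for CT reports, and the patient survey's answers on waiting for CT results run from under a week to more than two weeks. The request or images may exist well before the report.
- A reader might infer that only the intervention arm is affected. The off-protocol route rules that out. The planned sensitivity analysis excluding off-protocol cases does not help here, because it leaves the ordinary intervention CTs in place.
- A reader might take 95.4% rising to 99.8% as the estimate. It is the full-exposure value at that sensitivity, with every flagged cancer having a CT that is seen and followed.
- The radiographer's own reads are not contaminated; only the comparator can gain. No between-arm comparison of consultant accuracy is stated.

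**Conclusion.** The point holds as a possibility that the written plan leaves open. The consultant read is masked to one document but not to the imaging that document may set in motion, and that imaging may include the index diagnosis. If consultants use it, the radiographer-versus-consultant comparison is likely to tilt against radiographers, with unequal exposure between arms.

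The size cannot be known from the documents. Under the stated assumptions it runs from 0 to about 4.8 extra cancers called by consultants among about 25, and is about 1.1 if consultants have 95.4% sensitivity and exposure is complete. These figures rest on independent errors, on examination-setting sensitivity carried over to practice, and on all of the hospital's cancers arriving through a GP film. If fewer do, the counts shrink in proportion. With so few discordant cancers expected, a shift of one or two films would still matter to the comparison.

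The primary outcome, time from CXR to treatment or discharge, is not affected by this mechanism. This is an inexpensive improvement to a secondary outcome, not a flaw in the main comparison.

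**What to change.** In the section on the consultant radiologist CXR report, state that the study read uses the index CXR and earlier imaging only, and is masked to the radiographer's report, any CT request and any imaging acquired after the index CXR.

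Where masking is not feasible on the PACS in use, record at each read whether a later CT was available or had been seen, and report the accuracy comparison with a sensitivity analysis excluding those films.

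It is not necessary to bar the consultant who reports the CT from the study read of the CXR; that is a staffing preference.

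The cost is setting up a worklist, one recorded item per read, and fewer films in the sensitivity analysis. No additional reads are needed and patient care does not change. Masking is the better option: the films excluded would mostly be ones the radiographer flagged, so the sensitivity analysis removes radiographer true positives selectively. It can show whether the result depends on exposed reads, but it is not an unbiased estimate.

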### Comparison of radiographer and radiologist reports

The CXR reports generated by the reporting radiographers and consultant radiologists will be extracted, anonymised for source of report (radiographer/radiologist) and entered into a secure database using the unique study identifier. A respiratory physician will compare the reports for discrepancies, using a proforma with predefined criteria for clinically significant abnormalities. Discrepancies in observations, interpretations and recommendations will be highlighted. These criteria have been previously validated [32]. Report comparison will occur within three working days of the CXR examination.

### Additional radiology investigations

All additional radiology investigations will be organised by the radiology department following established departmental operating procedures. These additional investigations would be performed as part of routine clinical practice and will not require any additional radiation exposure. The reporting radiographers, after appropriate training, have been designated ‘non-medical referrers’ according to IRMER 2000 legislation.

### Repeat chest X-ray for suspected infection

According to British Thoracic Society (BTS) guidance [33], patients who have a CXR that is suspicious for infection require a follow-up CXR 6 weeks later following antibiotic therapy to ensure resolution. The reporting radiographer will arrange the follow-up CXR at the time of the initial CXR report for the immediate reporting arm, and the patient will be asked to re-attend the radiology department in 6 weeks. This will be communicated in the CXR report.

For patients who have a CXR suspicious for infection in the standard care arm the recommendation for a follow-up CXR in 6 weeks will be included in the report conclusion. This will be requested by the general practitioner, as is current practice.

### CT of the chest

Patients who have an abnormal CXR suspicious for cancer will have a CT of the chest performed. The reporting practitioner (reporting radiographer or consultant radiologist) will arrange this following standard department procedure. The CT scan forms part of routine clinical management and, therefore, does not require any additional radiation exposure. A consultant radiologist will interpret all CTs.

The CT performed will be stratified based on the CXR appearances and the likelihood of cancer. This will minimise radiation exposure, in line with best practice. For patients with a CXR that is suspicious but not categorical for lung cancer, a low-dose, unenhanced CT of the chest will be performed. For patients who have a CXR that shows a high likelihood of cancer, a CT of the chest and abdomen with intravenously administered contrast will be offered

### Index diagnosis by thoracic radiologist

Chest X-rays that are found to have discordant reporting radiographer and consultant radiologist reports at peer review will have an index diagnosis. For cases that have undergone a subsequent CT scan of the chest and abdomen, the CT report will constitute the index diagnosis. CXR reports, either reporting radiographer or consultant radiologist, will be deemed a true positive if CT confirms the CXR diagnosis and a false positive if the CT is normal or another pathology is demonstrated. True positive and true negative will be a consensus decision and corroboration between the CT and clinical history between a respiratory physician and a thoracic radiologist. Assessment of report accuracy will be made blinded to the origin (reporting radiographer/consultant radiologist) of the CXR report.

For cases that have not had a CT performed, an independent expert thoracic consultant radiologist will constitute the index diagnosis. The index radiologist will feed back the diagnosis via a standardised proforma. All available thoracic imaging (X-ray, CT) for the patient will be sent via the Image Exchange Portal (IEP) to the Royal Brompton Hospital. IEP is an established, secure method of transferring radiology cases for external review within the NHS. A thoracic consultant radiologist will review the available imaging and provide the definite diagnosis. CXR reports, both reporting radiographer and consultant radiologist, will be deemed a true positive if the thoracic radiologist confirms the CXR diagnosis and a false positive if the thoracic radiologist interpretation is normal or another pathology is demonstrated.

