### Outcome measures

The primary outcome is to test the impact of radiographer immediate reporting of GP CXRs, with immediate CT where appropriate, on time from performance of the CXR to treatment (with intermediate time points)/discharge for lung cancer.

Secondary outcome measures include:Measurement of the effect on the speed of the lung cancer pathway:
(i)6-and 12-month survival (lung cancer and all-cause)(ii)Number of emergency admissions for lung cancer(iii)Performance status at time of decision to treat(iv)Stage at diagnosis of lung cancer
Measurement of the effect of the pathway on efficiency including:
(i)The impact of immediate GP CXR reporting on the number of urgent respiratory cancer (2WW) referrals(ii)The accuracy and usefulness of radiographer CXR reporting in clinical practice(iii)The cost-effectiveness of radiographer reporting(iv)The influence of immediate GP CXR reporting, with immediate CT where appropriate, on the number of first 2WW appointments with all radiology results available
Measurement of the number of repeat CXRs performed in a timely fashion for suspected infectionThe effect of immediate reporting of GP CXRs on patient satisfaction

In addition to comparison as per randomisation within Homerton University Hospital, primary outcomes will be compared with a neighbouring hospital, Newham University Hospital.

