#### Health economic assessment

Adaptation of a health economic model that examined the impact of radiographer CXR reporting on the lung cancer pathway will be performed [35]. The model for this project will map out the care pathways following standard reporting and immediate reporting. It is assumed that differences in time to treatment will affect severity and, hence, costs and quality of life. Costs will be calculated from an NHS perspective, covering a 1-year period, and include X-ray reporting time, CXR cancer and non-cancer diagnostic accuracy, subsequent care costs, as well as reading and supervision costs. The cost per case detected will be reported. Quality-of-life scores will be obtained from the academic literature for different cancer stages and these will be used to generate quality-adjusted life years (QALYs). One-way and probabilistic sensitivity analyses will be conducted to assess the impact on costs and cost-effectiveness of changing parameters in the model. Due to the timing of the intervention in relation to the lung cancer pathway there may be no meaningful difference in QALYs for the internal comparison. The reduction in time to a non-lung cancer diagnosis may be a worthwhile improvement in quality of life.

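### The index diagnosis is limited to discordant report pairs, so cancers missed by both readers go unverified and absolute sensitivity cannot be validly estimated

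*Protocol article*

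**What the plan says.** Both readers report every eligible film. The section on the reporting radiographer report covers the radiographer; for the radiologist, the protocol states that "All CXRs will receive a consultant radiologist report", blinded to the radiographer's report. Under Comparison of radiographer and radiologist reports, "A respiratory physician will compare the reports for discrepancies".

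The section Index diagnosis by thoracic radiologist then fixes who gets a reference standard: "Chest X-rays that are found to have discordant reporting radiographer and consultant radiologist reports at peer review will have an index diagnosis". Two branches follow. With a CT, "For cases that have undergone a subsequent CT scan of the chest and abdomen, the CT report will constitute the index diagnosis". Without one, "For cases that have not had a CT performed, an independent expert thoracic consultant radiologist will constitute the index diagnosis". The section defines true and false positives and mentions true negatives, settled by consensus. It does not define a false negative. No section describes an index diagnosis, a sample audit or follow-up for pairs that agree.

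Accuracy is used in two places. Outcome measures lists as a secondary outcome "The accuracy and usefulness of radiographer CXR reporting in clinical practice". The Health economic assessment says that the model's costs will "include X-ray reporting time, CXR cancer and non-cancer diagnostic accuracy".

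**The concern.** This is partial verification. Both readers look at the same image, so a subtle cancer that one misses may well be missed by the other. Such a case is concordant, receives no index diagnosis and cannot enter the denominator of sensitivity.

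The discordant pairs can be used in two ways to give a sensitivity, and neither is valid. Counting agreement as correct biases the result upward. Restricting to discordant pairs biases it far downward: two equally good readers would each score 50%, whatever their true performance.

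At stake is a secondary outcome that readers may use to judge radiographer reporting. A cost model that includes diagnostic accuracy and reports cost per case detected would also rest on it.

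**Working it through.** The protocol gives no target, formula or sample size for accuracy, so there is no figure of its own to reproduce. The check is how far apparent sensitivity departs from true sensitivity under the stated verification rule.

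**Inputs from the protocol.** Radiographer sensitivity 95.4% and specificity 95.9% (Background; an end-of-training examination of 100 films, used here only as an illustration). About 50 lung cancers a year at the intervention hospital (Sample size).

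**Assumptions not in the protocol.** The radiologist is as accurate as the radiographer. An alternative true sensitivity is 80%. The dependence c between the readers' errors is 0, 50% or 90% of its maximum. Where prevalence matters, it is 1%. For the counts, all 50 cancers are taken to have had a study film.

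**Step 1: joint misses.** For two readers with sensitivity s, the proportion of cancers missed by both is m = (1 − s)² + c·s(1 − s).

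- s = 0.954: 0.046² = 0.0021 and s(1 − s) = 0.0439, so m = 0.0021, 0.0241 and 0.0416.
- s = 0.80: 0.2² = 0.04 and s(1 − s) = 0.16, so m = 0.04, 0.12 and 0.184.

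**Step 2: apparent sensitivity if CT resolves shared positives.** Only joint misses are lost, so apparent sensitivity = s/(1 − m).

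| Dependence c | True 95.4% | Joint misses of 50 | True 80% | Joint misses of 50 |
|---|---|---|---|---|
| 0 | 0.954/0.9979 = 95.6% | 0.1 | 0.80/0.96 = 83.3% | 2 |
| 50% | 0.954/0.9759 = 97.8% | 1.2 | 0.80/0.88 = 90.9% | 6 |
| 90% | 0.954/0.9584 = 99.5% | 2.1 | 0.80/0.816 = 98.0% | 9.2 |

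Specificity stays at about 95.9% in this case.

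**Step 3: apparent values if all agreement is taken as correct.** Shared false positives now count as true positives. At 1% prevalence and across the three values of c, a true 95.4% appears as 96.2%, 99.3% and 99.9%, and a true 80% as 85.8%, 97.3% and 99.6%. A true specificity of 95.9% appears as 96.1%, 98.0% and 99.6%.

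**Step 4: the comparison between readers.** In step 2 both readers' sensitivities are divided by the same 1 − m, so their ratio is unchanged. For unequal readers with sensitivities of 90% and 95.4%, strong dependence gives 2.09 joint misses in 50, or m = 0.042. The true difference of 5.4 points then appears as 5.4/0.958 = 5.6 points. A test on the discordant pairs does not use the missing cases.

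**The case against.** The protocol never announces an absolute sensitivity or specificity. The Background frames the aim as a comparison with radiologists, and the reports are compared in source-blinded pairs. For that purpose, resolving only the discordant pairs is a sound economy. The article refers to a full protocol (version 1.5) that is not shown and may hold the accuracy calculation.

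A reader might infer that the plan counts agreement as truth and will therefore report inflated accuracy. The text does not state that rule, so the overstatement is conditional. What stands is that the article itself fixes who is verified, and that rule leaves joint misses out of any sensitivity estimate.

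A reader might also infer that shared false positives are lost for good. The section CT of the chest says otherwise for cancer: "Patients who have an abnormal CXR suspicious for cancer will have a CT of the chest performed". A CT result will usually exist for these cases and could be used. The index-diagnosis section, however, does not use it when the reports agree. Nor does routine CT help with joint misses, because neither report prompts one.

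On size, the only sensitivity in the document combined with independent errors gives a shift of 0.2 points. Larger shifts need correlated errors or a lower true sensitivity, and the document quantifies neither.

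On the cost model, radiographers report in both randomised arms, so their accuracy is largely common to the internal comparison, and sensitivity analyses are planned. This limits the harm. It does not make an invalid input valid, least of all for cost per case detected.

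**Conclusion.** The point holds as a limit on what the accuracy outcome can claim. Discordant-only verification supports a paired comparison of the two readers. It does not support absolute sensitivity for either of them, and it supports absolute specificity only if existing CTs are also used for agreed positives, and then only for cancer.

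With CT resolving shared positives, sensitivity would be overstated by about 0.2 to 4 points at a true 95.4%, and by about 3 to 18 points at an assumed true 80%. These ranges rest on equal readers and on assumed dependence from none to 90% of its maximum. The direction is upward throughout; the size is unknown because the protocol gives no correlation between readers' errors.

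The primary time outcome is untouched and the relative comparison is not materially affected. Severity is moderate: a secondary outcome in a study that calls itself a pilot, with a knock-on to the cost model.

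**What to change.** 1. Keep the index diagnosis for discordant pairs as planned, and name the paired radiographer-radiologist difference (for example by McNemar's test) as the accuracy result.
2. For lung cancer, also score every film, concordant pairs included, against CT reports that already exist and against the lung cancer diagnoses the trial must identify for its own endpoints, within a fixed follow-up such as 12 months. Define a false negative explicitly on that basis.
3. State the limits of that follow-up. It may count cancers not visible on the index film as reader misses, which biases sensitivity downward, and it may lose cancers diagnosed elsewhere. Show a shorter window as a sensitivity analysis.
4. For other pathology, report only the paired difference.
5. Claim no absolute sensitivity or specificity from discordant-only verification, and do not enter such figures in the cost model.

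**Cost.** No extra reader and no extra imaging. All index films must be linked to cancer diagnoses. The article does not describe that linkage, but the care team assigns a study identifier at the time of the X-ray, which should make it feasible. The price is that no absolute accuracy is available for non-cancer findings. If the linkage cannot be done, restricting the claim to relative accuracy and adapting the cost model is the minimum change, settled before analysis.
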